### **Study Outcome**

All clinical outcome measurements were obtained at the three-month follow-up. The primary outcomes included differences in the 6MWT, the SF-12 scores, and the frailty phenotype scores. Secondary outcomes comprised step speed, 30s-CST, grip strength, WC, BMI and changes in lipid profiles (TC, HDL-C, LDL-C, and TG) at 3 months.

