## **Study Purpose**

**Primary Objective:** To assess improvement in 6-minute walk test (6MWT), 12-item Short Form Health Survey (SF-12) scores, and frailty phenotypic scores in UA patients undergoing PCI at 3 months postoperatively.

**Secondary Objectives:** To evaluate the changes in gait speed, 30-second chair stand test (30-s CST), grip strength, waist circumference (WC), body mass index (BMI), total cholesterol (TC), high-density lipoprotein cholesterol (HDL-C) levels, low-density lipoprotein cholesterol (LDL-C) levels, and triglycerides (TG) levels were assessed three months after PCI in patients with UA.

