## Interim analyses

No interim analyses were planned or conducted.

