### ***Quality of Life***

The 12-item Short Form Health Survey (SF-12) was administered in this study. The SF-12 consists of 12 items and includes eight dimensions of general health (GH), physical functioning (PF), vitality status (VT), mental health (MH), somatic pain (BP), somatic role restriction (RP), emotional role restriction (RE), and social functioning (SF). The PF, RP, BP, and VT dimensions compose the physical component summary (PCS), and the GH, SF, RE, and MH dimensions compose the mental component summary (MCS). The scores of each dimension and the total PCS and MCS scores were calculated sequentially, with a total possible score of 100; higher scores indicate better self-perceived quality of life for patients.

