### **Statistical Method**

Statistical analysis was performed using R (4.2.0). Continuous variables are presented as the means  $\pm$  standard deviations if they followed a normal distribution, and differences between groups were assessed via t tests. Alternatively, continuous variables that did not follow a normal distribution are presented as medians (interquartile ranges), and group comparisons were performed using the Wilcoxon test. Categorical variables are reported as frequencies (percentages), and group differences were evaluated using either the chi-square test or Fisher's exact probability method. Statistical significance was considered when  $P < 0.05$ .

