## Discussion

Findings indicated that a multidimensional digital CR intervention improved functional status (FP, 6MWT, gait speed, and 30-s CST) and metabolic markers (TC, TG, and LDL-C) in patients with UA undergoing PCI within a relatively short period compared to standard management. These results emphasize the program's potential to enhance physical recovery and cardiovascular health. Significant time effects were also observed for grip strength, WC, BMI, and overall quality of life (physical and mental components), reinforcing the efficacy of digital interventions. This novel rehabilitation model provides CVD education, clarifies essential diagnostic procedures, provides exercise rehabilitation guidance, and supports home-based rehabilitation. Promoting physical activity, encouraging lifestyle modifications, and facilitating behavioral changes during recovery contribute to improved quality of life in patients with UA undergoing PCI.

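### Three unranked primary outcomes, an unnamed SF-12 score and no success rule leave the family-wise error of the primary claim uncontrolled: about 11-14% (three tests) or 13-19% (four) if any one win counts

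*Combined protocol and SAP*

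**What the plan says.** The Study Purpose section gives the primary objective as "To assess improvement in 6-minute walk test (6MWT), 12-item Short Form Health Survey (SF-12) scores, and frailty phenotypic scores" at 3 months. The Study Outcome section repeats the same three without ranking them: "The primary outcomes included differences in the 6MWT, the SF-12 scores, and the frailty phenotype scores".

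The Quality of Life section describes eight SF-12 dimensions grouped into PCS and MCS, and says "The scores of each dimension and the total PCS and MCS scores were calculated sequentially". It does not say which of these ten scores is the primary one.

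The Statistical Method section deals with variables one at a time. For normally distributed variables "differences between groups were assessed via t tests"; otherwise a Wilcoxon test is used. One general threshold applies: "Statistical significance was considered when" P is below 0.05. There is no alpha split, hierarchy, adjustment or all-must-succeed rule in that section or any other. There is also no sample-size calculation that might show which outcome the trial was built around.

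Repeated looks add nothing to the problem: "No interim analyses were planned or conducted".

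The document also contains conclusions. The Discussion reports improvement over standard management on the frailty phenotype, 6MWT and several secondary outcomes. It then adds: "Significant time effects were also observed for grip strength, WC, BMI, and overall quality of life (physical and mental components").

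**The concern.** With several primary outcomes, a plan has to say what counts as success. If all must be significant, testing each at 0.05 is safe. If one is enough, the chance of at least one false positive grows with the number of tests unless the threshold is tightened. This plan says neither, and it leaves open how many primary tests there are, because SF-12 scores could mean one summary, both, or more.

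The Discussion shows why this matters in practice. A favourable conclusion is drawn from two of the three primaries against standard management. The third, quality of life, appears only as a time effect, yet it is presented as reinforcing efficacy. A change over time is not a between-group difference, and the Statistical Method section lists only two-group tests. A reader cannot tell which tests were confirmatory or what error rate stands behind the overall claim.

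**Working it through.** The documents state no family-wise error rate, so there is no figure to reproduce. The check computes what the written rules imply.

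**Inputs**
- Per-test threshold: 0.05 (Statistical Method). Sidedness is not stated; two-sided is assumed.
- Number of primary tests, k: 3 if one SF-12 score is used; 4 if both PCS and MCS are tested (Study Outcome, Quality of Life). The Discussion refers to physical and mental components, which makes 4 a natural reading.
- Correlation between test statistics, r: not given. A range from 0 to 0.7 is assumed, equal for all pairs.
- Success rule: not given. Any single significant primary is assumed to count.
- Truth: no effect on any primary outcome.

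**Independent tests.** P(at least one false positive) = 1 − (1 − 0.05)^k.
- k = 3: 1 − 0.95³ = 0.1426, or 14.3%.
- k = 4: 1 − 0.95⁴ = 0.1855, or 18.5%.

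The Bonferroni upper bounds, which hold under any correlation, are 3 × 0.05 = 15% and 4 × 0.05 = 20%.

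**Correlated tests.** For equicorrelated normal statistics with c = 1.96, the error is 1 − ∫ φ(u) [Φ((c − √r·u)/√(1−r)) − Φ((−c − √r·u)/√(1−r))]^k du, evaluated numerically:

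| r | 3 tests | 4 tests |
|---|---|---|
| 0 | 14.3% | 18.5% |
| 0.3 | 13.6% | 17.4% |
| 0.5 | 12.5% | 15.6% |
| 0.7 | 10.9% | 13.0% |

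Over r from 0.7 to 0 this gives about 11-14% for three tests and 13-19% for four. At r = 0.8 the values are 9.8% and 11.4%, still about twice 5%.

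**If all primaries had to succeed**, the error would be at most 5% with no adjustment.

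**Effect of a correction.** Bonferroni at 0.05/4 = 0.0125 gives 1 − (1 − 0.0125)⁴ = 4.91% for four independent tests, and never more than 5%. Holm starts at the same threshold and also controls the rate at 5% under any correlation.

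**Power cost.** Two-sample t test, 68 per arm (Randomization section), 134 degrees of freedom, noncentrality d·√(68/2), 80% power: the detectable d is 0.484 SD at 0.05 and 0.579 SD at 0.0125. This is an approximation, because the plan allows Wilcoxon tests and the frailty score is a short count of indicators.

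**The case against.** The strongest reply is that the plan never says one significant primary makes the study positive. If all had to succeed, there would be no inflation. The Discussion reports outcome by outcome, which is compatible with an any-win rule but does not establish it. This stands: the error figures are conditional on that reading. It does not remove the point, because the plan offers no all-must-succeed rule either, and the written conclusion is favourable without a stated between-group result on quality of life.

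Three stronger readings are tempting but unsupported.

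- A reader might infer that the plan promises 5% overall and breaks that promise. It does not: 0.05 is given as a general per-test threshold, and no family-wise claim is made.
- A reader might count all ten SF-12 scores with 6MWT and frailty as twelve independent primary tests and arrive at 1 − 0.95¹² = 46%. Independence is impossible here, since PCS and MCS are composed from the dimensions, and nothing says the dimensions are tested as primaries. That figure should not be used.
- A reader might treat the independence values as the answer. Some correlation is plausible: the frailty phenotype contains a walking-speed item and 6MWT is also a walking measure. The range should therefore reach down to the correlated values.

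It is also fair to say that multiplicity is not the only threat to the P values. Groups were formed by admission date, and only patients with complete data were analysed. Holm repairs neither. That limits what the correction achieves, but does not justify leaving the error rate undefined.

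**Conclusion.** The point holds in a conditional form. The plan leaves undefined which SF-12 score is primary, how many primary tests there are, and what constitutes success, and it controls no family-wise error. If any single win counts and there is no true effect on any primary, the chance of at least one false primary claim is about 11-14% with three tests and 13-19% with four, for assumed correlations from 0.7 to 0. Stronger correlation would lower these values, and an all-must-succeed rule would hold the error to at most 5%. The figures take each P value as valid in itself and say nothing about bias from non-random allocation or the completers-only analysis.

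**What to change.** Define the primary family as the between-group comparisons at 3 months of four scores: 6MWT, PCS, MCS and the frailty phenotype score. State the exact contrast for each, so that a within-group time effect cannot stand in for a group difference. Apply Holm to the four P values at overall two-sided 0.05: compare the smallest with 0.05/4 = 0.0125, the next with 0.05/3, then 0.05/2, then 0.05, stopping at the first failure.

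Matching is complete and conclusions are already written, so naming the family now is a choice made with results available. Say so, label the Holm analysis post hoc, and revise any primary claim that does not survive. Report the eight SF-12 dimensions and the nine secondary outcomes as estimates with 95% confidence intervals, without confirmatory claims.

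The cost is a short addition to the analysis text, a re-reading of the written claims, and some power: at Holm's strictest step the effect detectable with 80% power rises from about 0.48 to 0.58 SD at 68 per arm (t-test approximation). No new data are needed.

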### ***Physical Fitness***

The assessment of physical fitness parameters, including grip strength, walking speed, and balance, was conducted at two time points: upon admission and at the three-month follow-up. ① Grip strength was measured via an electronic grip device (manufacturer model: Guangdong Zhongshan Xiangshan Scale Instrument Co., Ltd. EH201R). During the measurement, a sitting position was maintained, the upper limbs naturally drooped at the side of the body, the palm faced the body, the grip metre handle faced outwards, the grip posture was adjusted according to palm size of the palm, and the grip metre was forced for measurement. A stable attitude was maintained during the measurement, and the grip metre was not swung back and forth. The grip strength of the dominant hand was measured 3 times, and the maximum value was taken as the final measurement result. ② Step speed: 4.6 m. The investigator used a stopwatch (model: new Dragon XL-011) to measure step speed in "s" (to 2 decimal places). ③ 30-s chair standing test: A straight back chair (sitting height of 43.2 cm) was used, and the patient was informed of the evaluation process and shown the movement before the test. The seat was placed against the wall, and the patient sat in a chair with their back straight, feet flat on the ground, and arms and

wrists crossed and held at the chest. When the test began, the patient completed 1-2 exercises, performed the preexperiment, and then started the timed test. The correct movement was as follows: completing the full standing position and then sitting down. If the patient's buttocks could touch the chair seat position, the above movements were repeated as much as possible within 30 s, and the effective number of movements was recorded. ④ BMI was calculated as follows:  $BMI = \text{body weight kg}/(\text{height m})^2$ ; and waist circumference per cm was measured.

### ***6-Minute Walking Test***

The 6-Minute Walking Test (6MWT), developed by Bakle, better evaluates the level of exercise tolerance and cardiac rehabilitation by measuring the distance walked in a defined period. The 6MWT was used to test cardiorespiratory function according to the guidelines of the American Thoracic Society. Each participant was asked to walk (not run) back and forth along a corridor as fast as possible to determine the longest possible distance walked within 6 minutes.

### ***Frailty***

The frailty phenotype (FP) was evaluated according to the following indicators: ① weight loss: weight loss of >5% or >4.54 kg in the past year; ② decreased gait speed (based on the calculation of gait speed according to a 4.57-m walking time): male height  $\leq 173$  cm: gait speed  $\geq 7$  s; height >173 cm: gait speed  $\geq 6$  s; female height  $\leq 159$  cm: gait speed  $\geq 7$  s; height >159 cm: gait speed  $\geq 6$  s; ③ decreased grip strength according to the corresponding sex and BMI range: gait speed  $\geq 7$  s; height >159 cm: gait speed  $\geq 6$  s; female height  $\leq 159$  cm: step speed  $\geq 7$  s; height >159 cm: step speed  $\geq 6$  s; ④ grip strength: measured according to the lower limit of grip strength within the range of the corresponding sex and BMI and the strength of the dominant hand measured with a grip strength device; ⑤ self-reported fatigue; and ⑥ physical activity level: male <383 kcal (approximately 2.5 h of walking); female <270 kcal (approximately 2 h of walking). The debilitation was diagnosed if 3 or more indicators were met, and predebilitation was diagnosed if 1 or 2 indicators were met. The FP is mainly used for routine screening of the degree of debilitation in hospitalized patients.

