The advantage of the multidimensional digital cardiac rehabilitation intervention package lies in its ability to provide personalized interventions tailored to each patient's specific condition, encompassing multiple aspects such as exercise, medication management, and nutrition guidance. The exercise training design not only helps improve cardiovascular function but also enhances muscle endurance, restoring the patient's ability to perform daily activities. The medication management dimension ensures that patients take their medications correctly and on time, reducing the occurrence of adverse drug reactions. Nutrition guidance assists patients in managing their weight and lowering blood lipids through appropriate dietary interventions, thus reducing the risk of cardiovascular disease recurrence. Psychological support, sleep management, and smoking cessation support help patients overcome the psychological stress caused by illness, improve sleep quality, and eliminate unhealthy lifestyle habits. These integrated interventions effectively improve the patient's overall health and contribute to the long-term maintenance of cardiovascular health.

Furthermore, this study places particular emphasis on the implementation of prehabilitation training, starting during hospitalization, which allows patients to become familiar with standardized rehabilitation content early on. During this process, the patients' family members were also included in the rehabilitation training program, ensuring they can provide essential support and enhance the role of health education within the home environment. These interventions collectively contributed to improvements in the patients' physical function, frailty, and lipid levels, while also enhancing their mental health and quality of life.

From a clinical application perspective, the digital rehabilitation package not only overcomes the temporal and spatial limitations of traditional inpatient treatment but also provides continuous and personalized rehabilitation support. Even after discharge, patients can continue to receive rehabilitation education, engage in self-management, and stay in contact with the medical team through the digital platform. This model is particularly beneficial for patients living in areas with limited access to medical

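### The frailty primary outcome lists six indicators but only five distinct components, so scoring it as written counts gait or grip twice against an unchanged 3-or-more cut-off.

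*Combined protocol and SAP*

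**What the plan says.** The Study Outcome section makes frailty a primary endpoint: "The primary outcomes included differences in the 6MWT, the SF-12 scores, and the frailty phenotype scores". The Frailty section then numbers six indicators:

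- Indicator 1, weight: "weight loss of >5% or >4.54 kg in the past year".
- Indicator 2, gait: "② decreased gait speed (based on the calculation of gait speed according to a 4.57-m walking time"), with limits of 7 s or 6 s by sex and height (men split at 173 cm, women at 159 cm).
- Indicator 3: "③ decreased grip strength according to the corresponding sex and BMI range: gait speed", followed only by limits of 7 s and 6 s and a height split at 159 cm. The first part names no sex; the second part is labelled female.
- Indicator 4: "④ grip strength: measured according to the lower limit of grip strength within the range of the corresponding sex and BMI". No kilogram values are given.
- Indicator 5, self-reported fatigue, with no question or threshold.
- Indicator 6, low physical activity, with kcal limits by sex.

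The classification rule follows: "The debilitation was diagnosed if 3 or more indicators were met". One or two indicators count as the intermediate (pre-frail) class. No score range or scoring sheet is given.

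On weight, the Study Rationale says of the programme: "Nutrition guidance assists patients in managing their weight and lowering blood lipids through appropriate dietary interventions". BMI and waist circumference are secondary outcomes.

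**The concern.** The heading and content of indicator 3 disagree, and neither reading gives a usable rule. By content it is gait again, duplicating indicator 2. By heading it is grip, duplicating indicator 4. Either way five components become six points while the cut-off stays at 3, so the duplicated component supplies two of the three points needed.

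Which component is doubled matters. The Discussion reports gait speed among the measures that improved against standard management, but mentions grip strength only under time effects. A score that doubles gait gives extra weight to something reported as responding, and gait is also a secondary outcome in its own right. A score that doubles grip does not. From the published definition a reader cannot tell which score was analysed, or reproduce it.

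The weight item raises a smaller question. Weight management is part of the programme, and the item does not separate intended from unintended loss. A patient who passes the threshold by following the advice gains a frailty point.

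**Working it through.** The documents give no frailty prevalence, score distribution or power figure, so there is no stated figure to reproduce. The check is on the scoring rule itself.

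**Inputs from the Frailty section.** Five distinct components (weight loss, slow gait, weak grip, fatigue, low activity); six numbered indicators; frail if 3 or more; intermediate class if 1 or 2.

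**Step 1: count patterns.** Five yes/no components give 2^5 = 32 patterns.

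- Each counted once: frail = C(5,3) + C(5,4) + C(5,5) = 10 + 5 + 1 = 16.
- One counted twice, and present: frail if at least one of the other four is present, 2^4 − 1 = 15 patterns.
- One counted twice, and absent: frail if at least three of the other four are present, C(4,3) + C(4,4) = 4 + 1 = 5 patterns.
- Total with one counted twice: 15 + 5 = 20.

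The 4 patterns that change are the doubled component plus exactly one other, which move from the intermediate class to frail. The lower boundary does not move: the doubled component alone scores 2 instead of 1, still intermediate. The count is the same whether gait or grip is doubled.

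**Step 2: illustrate the share classed frail.** Assumption, not in the documents: components are independent with equal prevalence p.

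- Counted once: F5 = P(Bin(5,p) ≥ 3).
- One doubled: F6 = p·P(Bin(4,p) ≥ 1) + (1 − p)·P(Bin(4,p) ≥ 3).
- The gap is the Step 1 pattern: F6 − F5 = p·4p(1 − p)³ = 4p²(1 − p)³.

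At p = 0.25: F5 = 0.1035; gap = 4 × 0.0625 × 0.4219 = 0.1055; F6 = 0.2090.

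| p | Counted once | One doubled |
|---|---|---|
| 0.15 | 2.7% | 8.2% |
| 0.20 | 5.8% | 14.0% |
| 0.25 | 10.4% | 20.9% |
| 0.30 | 16.3% | 28.7% |

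Under the by-content reading, the doubling is exact for women, because indicator 3 repeats their limits. For men it assumes that the fragment with no sex label repeats indicator 2.

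**Step 3: the outcome analysed.** The endpoint is a difference in scores. A doubled score equals the five-component score plus the doubled item. The between-group difference in mean score therefore changes by exactly the between-group difference in that item's prevalence. The documents give no component prevalences by group, so this cannot be evaluated.

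**Step 4: weight item.** It needs a loss above 5% or 4.54 kg, and by itself it places a patient only in the intermediate class. At a three-month visit, about 9 of the 12 months in its window precede the intervention.

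**The case against.** The strongest reply is that this is a drafting slip. Indicator 3 looks like the end of indicator 2 pasted under a grip heading. If staff scored five components once each, the data are unaffected. This is fair as far as it goes: a reader might infer that the frailty result was mis-scored, and the documents do not show that. The doubled item could be gait, grip or neither. What stands is that the written rule for a primary outcome cannot be applied as it is, and nothing elsewhere in the document resolves it.

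Three further stronger readings also fail:

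- The rise in the share classed frail (1.8 to 3.1 times across the table) might be taken as bias in the treatment comparison. It is not. It concerns a classification, under assumed prevalences and independence, and one rule applied to both groups creates no difference by itself.
- Indicators 2 and 3 might seem to contradict each other for a man of, say, 165 cm who takes 6.5 s. That needs the unlabelled fragment in indicator 3 to be the male rule, which the text does not say.
- The weight item might be read as counting any loss as frailty. The stated threshold contradicts that, and one indicator alone does not make a patient frail. The documents speak of managing weight and set no weight-loss target; most of the item's window precedes the programme; and any bias would run against the intervention. What remains is whether intent was recorded.

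**Conclusion.** The point holds as a defect in the written scoring rule of a primary outcome. Applied literally, the rule doubles one component, extends the range from 0–5 to 0–6, and moves 4 of 32 patterns from the intermediate class to frail (20 frail instead of 16). That count needs no prevalence assumption; under the by-content reading it does need indicators 2 and 3 to agree for each patient. The percentages in the table rest on independent, equally common components and are illustrative only. The size and direction of any effect on the between-group difference in scores are unknown. Confidence is high that the definition is wrong as written; whether the analysed data carry the error is undetermined. The missing grip cut-offs mean that even a corrected five-item list could not be scored from the text alone. The weight item is a secondary query of unknown size.

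**What to change.** 1. Remove the walking-time limits under indicator 3 and merge it with indicator 4, leaving five components scored once each: weight loss, slow gait, weak grip, fatigue, low activity. State the range as 0 to 5 and apply the 3-or-more rule to those five.
2. State the grip cut-offs by sex and BMI that were used, and the fatigue question and its threshold.
3. Confirm from the scoring records how baseline and three-month scores were derived. If any component was counted twice, re-score both time points and repeat the frailty analysis.
4. State whether weight-loss intent was recorded. If it was, count only unintentional loss; if not, add a sensitivity analysis of the score without the weight item.

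The cost is a text correction and, at most, re-scoring. The Physical Fitness section has gait and grip measured at admission and three months, and the Blood lipid indices section has height and weight recorded at admission and follow-up. No new measurement is needed, provided the item-level answers on weight loss, fatigue and activity were kept.
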